# Zhizhu Kuanzhong Capsule in treating patients with functional dyspepsia postprandial distress syndrome: study protocol for a multicenter, randomized, double-blind, placebo-controlled, parallel-group clinical trial

**DOI:** 10.1186/s13063-022-06396-5

**Published:** 2022-06-02

**Keywords:** Zhizhu Kuanzhong, Functional dyspepsia, Postprandial distress syndrome, Randomized controlled trial

## Abstract

**Background:**

Functional dyspepsia (FD) is one of the most common functional gastrointestinal disorders. Based on the various symptoms present in patients with functional dyspepsia postprandial distress syndrome (FD-PDS), routine agents such as acid suppressants, prokinetic drugs, and centrally acting drugs, offer limited treatment choices with potential side effects. As a preliminary clinical trial showed that the marketed product Zhizhu Kuanzhong Capsule (ZZKZ) can improve symptoms in FD-PDS patients, our study aims to provide further evidence on the clinical efficacy and safety of ZZKZ in the treatment of patients with FD-PDS.

**Methods:**

In this multicenter, randomized, patient- and investigator-blinded, placebo-controlled, parallel-group clinical trial, we will recruit patients with FD-PDS from 18 hospitals in China and Australia. The trial will enroll patients with FD-PDS based on the Rome IV diagnostic criteria. A total of 480 eligible patients will be randomized 1:1 into either ZZKZ or placebo group with 8 weeks of treatment and 4 weeks of follow-up. The primary endpoint will be measured by a self-rated Visual Analogue Score (VAS) for the degree of discomfort with both symptoms of postprandial fullness and early satiation, recorded once a day and 7 days a week. The primary analysis will aim to compare the response rate for FD-PDS VAS score between the groups before and after 8 weeks of treatment with an alpha level of 0.05 (2-sided).

**Discussion:**

This trial aims to strengthen the evidence for the efficacy and safety of ZZKZ, a marketed product, in treating FD-PDS. Compared to the previous clinical trial that targeted FD-PDS, this trial will have an 8-week double-blind treatment period to investigate the effect of long-term mediation through comparison with the placebo group.

**Trial registration:**

ClinicalTrials.gov NCT03825692. Registered on 28 January 2019

**Supplementary Information:**

The online version contains supplementary material available at 10.1186/s13063-022-06396-5.

## Background

Functional dyspepsia (FD) is one of the most common functional gastrointestinal disorders [1]. Patients can experience a range of dyspeptic symptoms, including postprandial fullness, early satiety, mid-epigastric pain, and mid-epigastric burning sensation. According to the symptom pattern, FD can be divided into two subtypes: postprandial distress syndrome (PDS) and epigastric pain syndrome (EPS) [1]. A cross-sectional population survey showed that the subtype distribution was 61% PDS, 18% EPS, and 21% overlapping variant with both syndromes [2]. An Italian epidemiological survey showed that 67.5% of patients diagnosed with FD had PDS, and 48% had EPS [3]. In Rome IV, it was noted that PDS is more common than EPS in clinical practice [4].

PDS originated from gastric motor dysfunction, including impaired gastric accommodation [5, 6], leading to a distal redistribution of a meal and, consequently, antral overload [7]. Based on the various symptoms present in patients with PDS, routine agents such as acid suppressants, prokinetic drugs, and centrally acting drugs offer limited treatment choice with potential side effects [8]. As PDS symptoms are prone to recur, safe and effective medications for long-term use become a critical concern for the patients and clinicians [9, 10].

Zhizhu Kuanzhong Capsule (ZZKZ) (National Medical Products Administration (NMPA) approval number Z20020003), manufactured by Shuangren Pharmaceutical Co., Ltd. of Lonch Group, has been marketed in China for more than 10 years and can be purchased in pharmacies or hospitals. ZZKZ is originated from the ancient document “Synopsis of Prescriptions of the Golden Chamber,” which mainly composed of 4 kinds of Chinese herbs: Rhizoma Atractylodis Macrocephalae, Fructus Aurantii Immaturus, Radix Bupleuri, and Fructus Crataegi. These herbs have long been applied in traditional Chinese Medicine (TCM) to alleviate gastrointestinal symptoms. In a multicenter clinical trial in China which applied Cisapride as control, 403 cases (105 cases in the control group, 196 cases in the treatment group, and 102 cases in the open group) were investigated [11]. The results showed that ZZKZ alone could relieve FD symptoms with an overall response rate of 89.2%. In a double-blind, randomized, placebo-controlled study of 392 subjects in 2017, ZZKZ was found to significantly improve symptoms such as early satiety and postprandial fullness discomfort in patients with FD-PDS [12].

ZZKZ also exhibited therapeutic effects on anxiety and depression through animal experiments and clinical studies. An animal study showed that ZZKZ improved the depressive behaviors of the animals, which the mechanism may be associated with the improvement of 5-HT neuron transmission and the inhibition of stress-induced corticoid secretion [13]. A multicenter clinical study of 202 patients showed that ZZKZ reduced the depression score in patients with FD-PDS and improved the depressive symptoms [14]. Another study showed that in patients with FD accompanied with anxiety and depression, there was no significant difference between the 4-week ZZKZ group and the Domperidone plus Neurostan group in the improvement of anxiety and depression scores [15].

In this trial, a placebo will be selected as the control since placebo design makes the trial easier for researchers to assess the side effects of ZZKZ and reduce biases through comparison of the groups. With evidence from the preliminary clinical trial that investigated the short-term use of ZZKZ [11, 12, 14–16], clinical studies on the effects of long-term ZZKZ use, including the degree of improvement in PDS symptoms, improvement in anxiety and depression, and safety of long-term efficacy, are still lacking. Aiming to consolidate the short-term evidence and explore the effect of long-term use of the medication, we design this trial to evaluate the clinical efficacy and safety of ZZKZ in the treatment of FD-PDS.

### Objectives

The study aims to evaluate the clinical efficacy and safety of the trial drug, ZZKZ, in the treatment of patients with FD-PDS.

## Methods and analysis

### Trial design

This multicenter, randomized, patient- and investigator-blinded, placebo-controlled, parallel-group study will be conducted at 18 hospitals in China and Australia. Patients fulfilling the Rome IV FD-PDS criteria [17] will be recruited primarily through advertisements on hospital websites and outpatient clinics. Before randomization, all patients will be required to provide written informed consent. In response to the COVID-19 pandemic, face-to-face site visits may be replaced by telephone consultations, and study materials may be distributed and returned via mail. The study protocol (version XYYY-V-2.1) has been approved by ethics committees at all participating hospitals following the Declaration of Helsinki and is reported based on SPIRIT (Supplementary file 1) [18]. This trial has been registered on ClinicalTrials.gov (NCT03825692). A flow diagram of the trial is shown in Fig. 1.

**Fig. 1 Fig1:**
[figure not shown]
Flow diagram of the trial

### Eligibility criteria

#### Inclusion criteria

(1) Outpatients aged 18–65 years; (2) meeting the Rome IV diagnostic criteria for FD-PDS; (3) able to discontinue prohibited medications that may affect the evaluation of the effectiveness; (4) with Visual Analogue Score (VAS) score ≥ 4 for major symptoms (at least one of postprandial fullness discomfort and early satiety); and (5) informed and voluntarily sign the informed consent form.

#### Exclusion criteria

(1) Gastroscopic findings of gastric cancer, peptic ulcer, erosive gastritis (grade 2 or higher), moderate to severe atrophic gastritis, dysplasia, or other organ gastrointestinal disease; (2) history of abdominal surgery (except for appendectomy and cesarean section); (3) defects in immune function, or using immunosuppressive agents or glucocorticoids within the past 3 months; (4) combined severe heart and lung insufficiency, liver and kidney dysfunction, an endocrine disorder, hematopoietic disorder, hematological tests revealed iron deficiency anemia; (5) severe anxiety or depression; (6) psychotic patients and those with intellectual or language disabilities; (7) pregnancy or breastfeeding; (8) allergy to the ingredients of the investigational drug; (9) drug or alcohol abuse; (10) participated in clinical trials in the past 3 months; (11) been regarded by the investigator as not feasible for this clinical trial.

#### Withdrawal and dropout criteria

Investigators and subjects both can initiate withdrawal, while investigator-initiated withdrawals include (1) if the subject’s condition continues to worsen during the trial, and continuation of enrollment may lead to a serious adverse event; (2) during the trial, the subject experienced certain comorbidities, complications, or special physiological changes; (3) in the trial, subjects’ poor compliance, automatic change of medication, or concomitant use of prohibited medicinal products as specified in the protocol affected the determination of efficacy and safety; (4) adverse events or serious adverse events occur, and the investigators determine it is inappropriate for the subject to continue to receive the test treatment; (5) during the trial, cases were unblinded for various reasons; and subject withdrawals at discretion include (1) the subject perceives the efficacy as poor; (2) intolerance to certain adverse reactions; and (3) whatever the cause, the subject is unwilling to continue to participate in the clinical trial.

All subjects who complete the informed consent form and are deemed eligible to enter the randomized trial through screening, regardless of the reason for withdrawal, will be considered dropout cases as long as they do not complete the observation cycle specified in the protocol. This will include both the subject’s voluntary withdrawal and investigator-initiated withdrawal.

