### Blinding

Both patients and investigators will be blinded to the assigned group. To achieve the blind method, the blind codes of this study which consist of two levels, will be held by the sponsor. The level I blind code will designate whether each drug number will be associated with drug A or drug B, respectively; the level II blind code will designate whether drug A and drug B will be a trial drug or a placebo. According to the statistical analysis plan, the level I blind code will not be revealed until the statistical analysis, which will be carried out by a statistical analyst. After the analyst writes a report, we will hold a concluding meeting, the level II blind code will be revealed for the first time on the spot, and the unblinded staff will sign on the blind code.

Unblinding will be permissible when serious adverse events occur and the actions to protect the safety of the subject must be taken immediately during the study. When urgent unblinding is required, the treating physician shall report to the principal investigator of the site. After approval, the emergency letter sent with the drug will be unpacked, the type of drug administered will be identified, a prompt rescue will be made, and the potential reasons will be clearly explained; the medical record will be signed and dated. Concurrently, the subject will be discontinued from the trial.

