### Concomitant drug

Long-term concomitant medication which may have treatment effects on PDS should be avoided:Medicines related to the treatment of PDS should not be administered during the study.Patients taking non-steroidal anti-inflammatory drugs such as aspirin before enrollment may continue taking these drugs without increasing or reducing the dose.Opioid preparations will be prohibited during the trial. If used before enrollment, sedative and hypnotic drugs (e.g., patients with insomnia take diazepam, etc., as needed) and antidepressants can be continued without increasing or decreasing the dose.Some antibiotics that affect gastric motility will be prohibited during the trial: macrolide antimicrobial or azole antifungal.During the trial, acupuncture, massage, cupping, and other TCM therapies related to the treatment of this disease shall not be used.If the participant is eligible by the inclusion criteria but needs to continue taking medicine or to add other drugs or treatment methods for the consideration of comorbid illness or changes of illness state, it will be necessary to record all information to the case report form, including the name of the drug (or other therapies), the dosage, use frequency, and time.

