### Statistical analysis

Statistical analysis will be performed using SAS 9.3 software by an independent statistician. All statistical tests will use a two-sided test, *P* ≤ 0.05 will be regarded as significant. A 95% confidence interval will be used. Based on the intention-to-treat principle, the missing data will be replaced by the last data (i.e., the missing efficacy data will be replaced by the efficacy data of the previous follow-up). The efficacy analysis will be mainly based on a full analysis set, and the central effect will be considered. The primary efficacy endpoint will be tested for superiority. The efficacy between groups will be compared using the Cochran-Mantel-Haenszel-*χ*^2^ test with and without regard to center stratification, and a 95% confidence interval of the difference between groups will be calculated. Method repetitive measure analysis of variance will be used to analyze the secondary outcome of VAS scores at different time points between groups. Sub-analysis will be carried out to review whether there is a difference in the effect of ZZKZ according to demographical data across countries. The safety analysis will be mainly based on descriptive statistics. The adverse events that occur in this trial will be described in a list, and the incidences will be compared using Fisher’s exact probability test.

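### The withdrawal rules do not separate stopping study drug from stopping observation, so week-8 primary data can be lost avoidably, for reasons plausibly linked to outcome

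*Protocol article*

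**What the plan says.** **Withdrawal and dropout criteria.** The investigator-initiated withdrawals include, as item (3), poor compliance, the patient changing medication on their own, or "concomitant use of prohibited medicinal products as specified in the protocol affected the determination of efficacy and safety". Item (5) is that "during the trial, cases were unblinded for various reasons". Patients withdrawn for any reason "will be considered dropout cases as long as they do not complete the observation cycle specified in the protocol", and this covers "both the subject’s voluntary withdrawal and investigator-initiated withdrawal".

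**Blinding.** After an emergency unblinding: "Concurrently, the subject will be discontinued from the trial".

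**Concomitant drug.** The prohibitions reach treatments for the trial disease: "Medicines related to the treatment of PDS should not be administered during the study".

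**Statistical analysis.** "Based on the intention-to-treat principle, the missing data will be replaced by the last data", which the section explains as taking the value from the preceding follow-up. "The efficacy analysis will be mainly based on a full analysis set".

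**Primary outcome.** Response is a 50% fall from baseline, at week 8, in the weekly average of self-rated daily diary scores.

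**The concern.** Stopping study drug and stopping observation are different events, and the article treats them as one. Item (4) of the investigator list shows this: a judgement that further test treatment is inappropriate is itself a ground for leaving the trial.

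Intention-to-treat needs more than keeping everyone in the analysis set. It also needs the outcome to be sought from everyone, whatever their adherence. Under these rules non-adherence is a reason for withdrawal, and the missing week-8 score is then replaced by an older one.

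The loss is plausibly tied to outcome. A patient whose symptoms persist is likelier to take a PDS medicine, and urgent unblinding follows a serious adverse event. Item (3) applies only where the breach interfered with judging efficacy and safety, so investigator judgement also decides who leaves. If withdrawal differs by arm, the comparison of week-8 response rates can shift. A patient who improves early, relapses and then takes a prohibited PDS drug could be carried forward as a responder.

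**Working it through.** **1. The rules side by side.**

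| Trigger | Ground for withdrawal? | End of observation stated? |
|---|---|---|
| Poor compliance, self-changed medication, prohibited drug | Yes, item (3), if it interfered with the assessment | No; inferred from withdrawal and the dropout definition |
| Unblinding for any reason | Yes, item (5) | No; inferred in the same way |
| Emergency unblinding | Yes | Yes, in Blinding |

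For none of these does the article describe diary collection after withdrawal.

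**2. The plan's own allowance.** Inputs from Sample size calculation: 187 per arm, 20% dropout, 480 in total.
- 187 / 0.80 = 233.75, so 234 per arm and 468 in total. The plan's 480 (240 per arm) is within 3% of this.
- Dropouts allowed for: 0.20 × 480 = 96, or 48 per arm, leaving 192 per arm.
- At 54% versus 38%, 192 per arm gives 88.5% power. The allowance therefore protects power. It does nothing about bias.
- The 187 itself does not reproduce from the stated rates, alpha and power (the pooled two-proportion formula gives 152). That is a separate matter and does not enter here.

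**3. Bias from carrying forward.** The documents give no withdrawal rates by arm or reason, so every rate in this step is an assumption. Let d_Z and d_P be the shares withdrawn on ZZKZ and placebo. Let l be the share of withdrawn patients counted as responders by the carried value, and r the share who would be responders if week 8 were observed, both the same in each arm. Then

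bias in the difference = (d_Z − d_P) × (l − r)

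| d_Z, d_P | l | r | Bias |
|---|---|---|---|
| 15%, 25% | 20% | 20% | (−0.10)(0) = 0 |
| 15%, 25% | 20% | 40% | (−0.10)(−0.20) = +2 points |
| 15%, 25% | 20% | 50% | (−0.10)(−0.30) = +3 points |
| 15%, 25% | 10% | 50% | (−0.10)(−0.40) = +4 points |
| 20%, 20% | any | any | 0 |

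Only the gap matters, so 10% versus 20% gives the same results. A positive sign favours ZZKZ. The direction is not fixed: swapping l and r in the second row gives (−0.10)(+0.20) = −2 points.

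**4. Outer limit.** Suppose a share d of each arm is unobserved for any reason and completers respond at 54% and 38%. The full-population difference then lies within (1 − d) × 16 ± 100d points:
- d = 5%: 15.2 ± 5, or +10.2 to +20.2
- d = 10%: 14.4 ± 10, or +4.4 to +24.4
- d = 20%: 12.8 ± 20, or −7.2 to +32.8

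The lower limit reaches zero at d = 0.16 / 1.16 = 13.8%. These are logical bounds, not estimates. They cover all missing data, including patients who withdraw consent and cannot be recovered.

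**The case against.** **Most of the loss is inferred.** Only the Blinding section says outright that a patient leaves the trial, and only for emergency unblinding. The dropout definition is conditional: a withdrawn patient is a dropout if the observation cycle is not completed. The full protocol may describe follow-up after withdrawal. This stands as a limit on certainty. It does not remove the point, because the article explicitly ends participation in one case and never makes the distinction in the others. Data not collected cannot be restored by a later analysis plan.

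**A reader might infer that the plan contradicts intention-to-treat or excludes withdrawn patients.** The documents do not support that. The analysis uses a full analysis set with missing values filled, and nothing says withdrawn patients are removed from it. The weakness is incomplete follow-up.

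**A reader might also attribute all 96 dropouts to these rules, or set 20% missing against the 16-point effect.** Neither is sound. The 96 covers every reason, voluntary withdrawal included, and these triggers may be a small part of it. A missing share is not a bias.

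**Persistent symptoms usually mean the carried value is already non-response.** True for many patients, and it limits the harm. However, such a patient may respond by week 8 after taking another medicine, and an early responder may relapse. Carrying forward can be wrong in either direction.

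**Outcome dependence is not shown for every trigger.** Poor compliance has many causes, and unblinding is probably rare. The link is strongest for prohibited PDS medicines.

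**Conclusion.** The point holds as a design weakness that should be corrected. As written, the withdrawal, blinding and analysis rules together allow week-8 diary data to be lost for non-adherence, prohibited medication and unblinding, and replaced by earlier scores. The loss is avoidable because the endpoint is self-rated at home.

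Its size is unknown. Bias of about 0 to 4 points rests on an assumed 10-point gap in withdrawal, carried-forward response of 10–20% and week-8 response of 20–50% among withdrawn patients. It is zero if withdrawal and response rates are equal across arms. The end of observation is explicit only for emergency unblinding and is inferred elsewhere, so confidence is moderate.

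**What to change.** Reconcile Withdrawal and dropout criteria, Blinding, and Statistical analysis on data collection:

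- Define stopping study drug and stopping observation as separate events. Patients who stop drug or are withdrawn for these reasons, and who have not withdrawn consent, continue the daily diary to week 8 on paper or eDiary, with telephone contact if needed.
- Record the date and reason of drug stop, prohibited-drug use and unblinding.
- Include the observed week-8 data of all randomised patients in the analysis.
- Counting prohibited PDS treatment before week 8 as non-response can be a prespecified sensitivity analysis. Making it primary is an estimand choice on which statisticians may differ.

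The clinical rules on who stops treatment are untouched.

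**Cost.** The eDiary, its text reminders and telephone consultations already exist, so the extra follow-up is modest. The change is still a formal amendment. Under Plans for protocol amendments it needs agreement between the sponsor and the principal investigator, then ethics approval, including at the sub-centres, in a trial of 18 hospitals in two countries. Recruitment began in October 2019 and was due to finish before December 2022. The benefit therefore reaches only patients not yet at week 8, and the trial would contain two data-collection regimes, which the report should state.

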### Randomization and allocation concealment

Stratified-block randomization method by SAS 9.3 statistical software will be used to centrally generate a random number table stratified within each participating hospital according to the number of cases allocated to each participating hospital with a ratio of 1:1 and will be performed by a statistician in a third institution. Parameters of the selected block’s length and the random initial seed will be sealed together as secret data in the blind codes.

### Implementation plan

Each drug will be randomly coded with an identification number according to the random number table and distributed to each site. Each site will further dispense the drug identification numbers according to the order of the subject’s visit and would not be able to alter the numbering arbitrarily.

